### Inclusion criteria

Male and female aged > 18Able to provide written informed consentASA grade I–IVPlanned posterior approach spinal surgery involving 2 or more levels in the lumbar or thoracic regions

#### Exclusion criteria

Absence of or inability to give informed consentPre-existing infection at block siteSevere coagulopathyAllergy to local anaesthesia (or any other contraindication to block performance, e.g. concern re local anaesthesia toxicity)Previous history of opiate abusePre-existing chronic pain conditionPre-existing dementia (due to the need to co-operate in completing QoR-15 score day after surgery)Surgery involving cervical vertebraeSurgery due to queried or confirmed malignancySurgery involving 5 or more vertebral levelsPostoperative admission to ICU for continued ventilation

### Standard care

Standard care will be identical in both groups. The only difference will be that one group will receive an erector spinae plane block and the other will not. Airway management strategy will be at the discretion of the treating anaesthesiologist. However, as patients will be in the prone position, all patients will be intubated with a reinforced endotracheal tube. Ventilation strategy, choice of haemodynamic monitoring and venous access will also be at the discretion of the attending anaesthesiologist. The haemodynamic goal will be to maintain systolic blood pressure within 20% of the baseline. Persistent intraoperative elevations above this point will trigger oxycodone administration intravenously. The frequency and dosage of this will be at the discretion of the treating anaesthesiologist.

### Concomitant medication

Post surgery, patients will be transferred to the post anaesthesia care unit (PACU) and then to ward level, once PACU discharge criteria are met. Patients will be prescribed oxycodone 1–2 mg IV as required for postoperative pain in PACU until the verbal rating scale (VRS) pain score is < 2 in accordance with our hospital policy. On discharge to the ward, all patients will be prescribed paracetamol 1 g IV 6 hourly, ibuprofen 400 mg orally 8 hourly and oxycodone immediate release 5–10 mg 2 hourly as required for rescue analgesia unless contraindicated. Ondansetron 4 mg PO/IV 8 hourly as required will be prescribed for treatment of nausea or vomiting in the PACU or on discharge to the ward. Remifentanil and ketamine will not be used in any patient enrolled in the study.

### Concomitant treatment

Surgery will be performed by suitably qualified and experienced spinal surgeons. Surgical technique will vary as deemed necessary for each case. No other forms of analgesia (e.g. intrathecal opioids, epidural analgesia) will be used during the trial.

### Study intervention

Participants randomised to the ESP group will receive an ultrasound guided bilateral ESP block post induction of general anaesthesia and prior to commencement of surgery. Blocks will be performed under full asepsis with patients in the prone position. Twenty millilitres of 0.25% levobupivacaine will be injected bilaterally at the level corresponding to the mid-point of the range of surgical dermatomes likely to be affected by the surgery. Typically, ESP will be administered at T6 level (total 40 ml). The ESP block will be performed as follows:

The approximate midpoint of the intended surgical incision will be identified first. The ultrasound transducer will then be placed approximately to 2–3 cm lateral to the midline in a longitudinal orientation to identify the hyperechoic line of the transverse process with its associated acoustic shadow. After identification of trapezius, rhomboid major and erector spinae muscle groups superficial to the transverse process, an echogenic needle will be advanced in a cranio-caudal direction. The needle tip will be advanced until it is located in the interfascial plane deep to the erector spinae muscle group and superficial to the transverse process. Once in position, 20 ml 0.25% levobupivicaine will be injected under ultrasound guidance. Correct needle tip position will be confirmed by the presence of linear spread between the transverse process and the erector spinae muscle group. The same process will then be repeated on the opposite side at the same vertebral level. Because patients will be under general anaesthesia during the block performance, no formal dermatomal sensory testing of block efficacy will be performed. Surgery will commence once the block is completed. There will be no further intervention to the routine conduct of surgery and anaesthesia after this point. Blocks will be performed by anaesthesiologists with subspeciality training in regional anaesthesia. To improve adherence to the intervention protocol, anaesthesiologists will be asked to document the block performance in the anaesthesiology patient record. Although the ESP has been established as a safe means of providing analgesia in spine surgery, we will make all our data available to local data monitoring committee.

### Patient and process characteristics

The following data will be recorded in the perioperative period:

#### Preoperative

AgeBMIPre induction blood pressure and heart rateIntended surgery

#### Intraoperative

Timing/duration of surgery anaesthesiaHaemodynamic parameters (highest and lowest BP and HR recorded)Total opioid given

#### Postoperative

Surgical or anaesthesia-related complications (including complications related to ESP block)Pain scores at rest and on movement at 6, 12 and 24 hAnalgesia use in the first 24 hTime to first analgesiaAntiemetic usageQoR-15 scoreLength of stay

All patient data collected will be handled in accordance with European Union General Data Protection Regulations (EU 2016/679).

### Outcome measures

Quality of recovery will be measured using the QoR-15 questionnaire. Postoperative pain will be quantified using a verbal response scale (VRS) ranging from 0 to 10, where 0 equals “no pain at all” and 10 equals “the worst pain imaginable”. Reported pain scores will then be plotted against time to give the AUC of pain versus time. Pain scores will be recorded at 6, 12 and 24 h post surgery at rest and on movement.

Postoperative complications will be graded using the Comprehensive Complication Index calculator (CCI^R^). This data will be acquired using our electronic patient record system to remotely track the progress of our patients in the postoperative period. Patient progression will be monitored for the entirety of their hospital stay or for 30 days post surgery (whichever is longer).

### Statistical considerations

Data will be inspected and tested for distribution according to the Kolmogorov-Smirnov test. Normally distributed data will be compared between study arms using the unpaired *t* test, whereas non-normally distributed data will be compared using the Mann-Whitney *U* test. All data will be summarised as mean + SD or median (25–75% range) as appropriate.

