#### Secondary aims

Secondary aims are to discover whether the ESP block has favourable outcomes on other metrics of patient-centred patient outcome: area under the curve (AUC) of VRS pain versus time at rest and on movement up to 24 h postoperatively, 24 h opioid consumption, time to first analgesia in recovery, length of stay (LOS) and incidence and severity of postoperative complications as measured by the Comprehensive Complication Index (CCI) score.

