### Sample size and justification

The primary outcome of this study will be the QoR-15 score at 24 h postoperatively. The established minimum clinically important difference in QoR-15 is 8.0 and the mean SD of QoR-15 scores after major spinal surgery is in the order of 14 [range of QoR score is 1–150]. Therefore, assuming type I error = 0.05 and type II error = 0.2 (80% power to detect this difference), then *n* = 25 patients will be required in each group. To accommodate for participants who may withdraw from the study, we will aim to recruit *n* = 26 patients to each study arm.

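### A Kolmogorov-Smirnov pre-test on the trial data chooses the test and summary for every outcome, so the primary effect measure is not fixed; time to first analgesia also lacks a rule for patients who need none

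*Protocol article*

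**What the plan says.** The Statistical considerations section of the protocol article is three sentences long and covers all outcomes. It opens with "Data will be inspected and tested for distribution according to the Kolmogorov-Smirnov test". If the data pass, the t test applies ("Normally distributed data will be compared between study arms using the unpaired"). If they fail, the rank test applies ("non-normally distributed data will be compared using the Mann-Whitney"). The section ends with "All data will be summarised as mean + SD or median (25–75% range) as appropriate". It gives no significance level for the pre-test and does not say whether the pre-test is run per arm, on pooled data or on residuals. It does not say whether the critical value allows for an estimated mean and SD.

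The Sample size section says "The primary outcome of this study will be the QoR-15 score at 24 h postoperatively". It sizes the trial from two inputs. For the target effect it says "The established minimum clinically important difference in QoR-15 is 8.0". For the spread, its assumption reads "the mean SD of QoR-15 scores after major spinal surgery is in the order of 14". This is a calculation for a difference in means.

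The secondary aims include "time to first analgesia in recovery". The list of postoperative data names time to first analgesia without limiting it to recovery. Under Concomitant medication, oxycodone in the post-anaesthesia care unit (PACU) is given only when pain calls for it, so a patient may leave the unit without a dose. The article names no time-to-event method and no rule for such a patient.

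**The concern.** This is a rule that the protocol states, not a detail left to an analysis plan. It has two weaknesses.

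First, what the primary analysis estimates depends on a preliminary test in the same data. If the pre-test accepts normality, the result is a difference in mean QoR-15 that can be read against 8 points. If it rejects, the result is a rank test reported with medians, which does not by itself estimate that difference. The branch depends heavily on which form of the Kolmogorov-Smirnov test the analyst's software runs, and the article does not say.

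Second, the same two tests are the only ones offered for time to first analgesia. A patient who needs none has no time to enter. Leaving such patients out would condition on something that happens after randomisation and that the block is meant to affect. Assigning them a value needs a rule that is not given.

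**Working it through.** **Inputs from the article.** Difference 8, SD 14, type I error 0.05, power 0.80, 25 per arm. Sidedness is not stated; two-sided is assumed.

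**The plan's own figure.** n per group = 2 × (1.960 + 0.842)² × 14² / 8² = 2 × 24.04 = 48.1, so 49 per group (38 if one-sided). The stated 25 is not reproduced. The same formula without the factor 2 gives 24.04, which rounds up to 25. At 25 per group the power of the t test is about 51%. This is a separate matter, but it explains why the simulated powers below lie near 50% rather than 80%.

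**How often the pre-test rejects one sample of 25** (simulated; pre-test level of 5% assumed):

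| Distribution | Estimated mean and SD, uncorrected | Lilliefors-corrected |
|---|---|---|
| Moderately left-skewed (reflected gamma, shape 2) | about 2% | about 40% (38% to 42% across runs) |
| Exponential | 6% to 8% | about 68% |

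The cause is the critical value. At n = 25 it is 0.264 uncorrected and 0.173 corrected.

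**What the two-stage rule does at trial level** (10,000 trials per scenario, SD 14, pre-test in each arm, Mann-Whitney if either arm rejects):

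| Scenario | Pre-test | Mann-Whitney chosen (8-point effect) | Type I error of rule | Power at 8 points: fixed t / fixed Mann-Whitney / rule |
|---|---|---|---|---|
| Normal | uncorrected | 0% | 5.1% | 51% / 47% / 51% |
| Normal | Lilliefors | 10.5% | 5.2% | 51% / 47% / 50% |
| Left-skewed | uncorrected | 3% | 4.9% | 52% / 64% / 53% |
| Left-skewed | Lilliefors | 64% | 5.2% | 52% / 64% / 62% |

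**How often the rule changes the verdict.** The rule departs from a fixed t test only when it picks Mann-Whitney and the two tests also disagree. With a true 8-point effect they disagree in 7.3% of normal and 15% of left-skewed trials. As a rough check under the Lilliefors version, treating the two events as independent:
- normal: 0.105 × 0.073 = 0.8%
- left-skewed: 0.642 × 0.150 = 9.6%

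Direct simulation gives 0% (uncorrected) to 1% (Lilliefors) for normal data, and 1% to 11% for left-skewed data.

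Heavier skew makes this larger. For a reflected lognormal (sigma 0.8), power is 59% with a fixed t test and 72% or 88% under the rule. The verdict therefore differs in at least 72 − 59 = 13% or 88 − 59 = 29% of trials. Type I error of the rule there is 5.2% or 4.8%.

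**Time to first analgesia.** The article gives no rate of patients without a dose, so this scenario is assumed throughout: 25 per arm, 10% non-events in controls, exponential times with mean 30 minutes among the rest in both arms, follow-up cut at 120 minutes.

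| Non-events, ESP arm | Mann-Whitney, events only | Mann-Whitney, non-events ranked last | Log-rank |
|---|---|---|---|
| 30% | about 5% | 22% | 34% |
| 40% | about 5% | 43% | 62% |
| 50% | about 5% | 68% | 84% |

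Restricting to patients with an event loses the whole effect here, because the arms differ only in the share who need a dose.

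**The case against.** The best defence of the primary analysis is that the gate rarely matters. If the uncorrected test is used and QoR-15 is near normal, the rule is in practice a t test, which is close to the recommended analysis. Type I error stays between 4.8% and 5.2%. Even always taking the smaller of the two p-values would raise it only to about 6.1% to 6.5%. This stands, and it limits the size of the point. It does not rescue the rule: a gate that almost never opens serves no purpose, and with the Lilliefors version it opens in most moderately skewed trials.

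Several stronger readings are tempting, and the documents do not support them:

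- A reader might infer an inflated false-positive rate. The simulations show none of note.
- A reader might take the 7% disagreement between the two tests as the effect of the rule. It is not, because the protocol does not run both tests and choose.
- A reader might infer that the Comprehensive Complication Index (CCI), length of stay and opioid use would routinely pass as normal. That depends on the unstated version. The data are also to be inspected, and a large share of zeros in CCI would show: with 60% zeros even the uncorrected test rejected 90% of simulated samples.
- A reader might say that a rank analysis can never be set against 8 points. Under a location shift a Hodges-Lehmann estimate can, but the article plans medians and no such estimate.
- A reader might infer that patients without a dose will be dropped. The article does not say so. If time to first analgesia covers any analgesic up to the ward, where paracetamol and ibuprofen are prescribed at regular intervals, nearly everyone has an event. Ranking non-events last also recovers much of the power.

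**Conclusion.** The point holds with moderate weight and should be corrected. The test and summary for QoR-15 are chosen from the trial data although the trial is sized on a mean difference, and the choice turns on an unstated version of the pre-test. The verdict changes relative to a fixed t test in about 0% to 1% of normal and 1% to 11% of moderately skewed trials, and in more under heavy skew. These figures assume a pre-test per arm at 5% and 25 analysed per arm. The distribution of QoR-15 in this population is not given.

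The time-to-first-analgesia part is conditional. It matters only if some patients need no as-required dose, and its power figures rest on assumed non-event rates. What is certain is that neither named test can include such patients without a rule that the article does not state.

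**What to change.** Remove the normality gate and name one analysis per outcome, before the randomisation key is released:

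- **QoR-15 at 24 h:** difference in means with 95% CI (t test, Welch test or linear model), read against 8 points. Mann-Whitney as a sensitivity analysis.
- **CCI, length of stay, 24 h opioid use:** Mann-Whitney with the Hodges-Lehmann difference and 95% CI.
- **Time to first analgesia:** define the event as the first as-needed opioid dose and state whether the window is recovery only or longer, since the aims and the data list differ. Keep all randomised patients. Use Kaplan-Meier and log-rank, with patients who have no event censored at a common fixed time such as 24 h. Censoring at PACU discharge is less suitable: discharge depends on meeting criteria and may be informative.

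The cost is a change of wording and slightly more analysis work. No extra patients are needed, and time to first analgesia and 24 h analgesia use are already on the data list. Nothing is lost if QoR-15 is near normal. If it is skewed, a fixed t test gives up some power: 52% against 53% to 62% under the gated rule with moderate skew, and 59% against 72% to 88% in the heavy lognormal case. The sensitivity analysis would show this.

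### The primary 24 h QoR-15 comparison is fixed as an unadjusted two-sample test although age and intended surgery are known before allocation is revealed; prespecified ANCOVA is a cheap improvement that may gain precision.

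*Protocol article*

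**What the plan says.** **Analysis.** Statistical considerations has one rule for all outcomes. A Kolmogorov-Smirnov test decides the branch: "Normally distributed data will be compared between study arms using the unpaired" t test, otherwise Mann-Whitney U. No covariate is named.

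**Baseline data.** The Preoperative list reads, with its items run together in the extracted text, "AgeBMIPre induction blood pressure and heart rateIntended surgery". Randomisation and blinding has the envelope opened after induction, so these items precede disclosure of allocation. That section uses blocks of 6 and names no stratification factor. It withholds the randomisation key from investigators until data collection is complete.

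**Case mix.** The inclusion criteria admit adults of ASA grade I to IV having surgery on at least 2 thoracic or lumbar levels. The exclusion criteria remove 5 or more levels, which leaves 2 to 4. Concomitant treatment adds: "Surgical technique will vary as deemed necessary for each case".

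**Baseline QoR-15.** The Discussion states that preoperative QoR-15 will not be assessed and accepts this as a limitation.

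**Sample size inputs.** "The established minimum clinically important difference in QoR-15 is 8.0"; "the mean SD of QoR-15 scores after major spinal surgery is in the order of 14"; "assuming type I error = 0.05 and type II error = 0.2 (80% power to detect this difference"). The stated result is 25 per group, with 26 to be recruited.

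**The concern.** Neither the randomisation nor the analysis makes any use of patient features known beforehand. If extent of surgery or age predicts 24 h QoR-15, its contribution stays in the error term, and a chance difference between arms in that feature is not corrected in the estimate. With about 25 patients per arm, a modest gain in precision is worth having. The natural covariate, baseline QoR-15, is ruled out by design, so age and intended surgery are among the few candidates left. Both are already on the record, so using them needs no extra patient and no extra measurement.

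At stake is the width of the interval for the primary outcome. The validity of the comparison is not in question.

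**Working it through.** **Inputs.** From Sample size and justification: difference 8, SD 14, type I error 0.05, 25 per group. Sidedness is not stated; two-sided is assumed. The R-squared of age and planned levels with 24 h QoR-15 appears nowhere, so a range of 0 to 0.25 is assumed.

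**1. The plan's own figure.** For two means, n per group = 2 × (1.960 + 0.842)² × 14² / 8² = 2 × 7.849 × 3.0625 = 48.1, so 49 (50 with the t distribution). One-sided it is 38 (39 with t). The stated 25 is not reproduced. Leaving out the factor of 2 gives 24.04, which rounds up to 25. This is a separate fault; here it only sets the starting power.

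**2. Unadjusted power at 25 per arm.** SE = 14 × √(2/25) = 3.96. Noncentrality = 8 / 3.96 = 2.02 on 48 df, critical value 2.011. Power is 50.8% (64% if one-sided).

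**3. Adjusted power, two covariates.** SE = 14 × √(1 − R²) × √(2/25) × √(1 + 2/45) on 46 df, critical value 2.013. The last factor (variance × 1.044) is the cost of estimating two coefficients with 50 patients: 45 = 50 − 2 − 3.

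| R² | SE | 95% half-width | Power | Change (points) |
|---|---|---|---|---|
| unadjusted | 3.96 | 7.96 | 50.8% | – |
| 0 | 4.05 | 8.15 | 49.0% | −1.8 |
| 0.05 | 3.94 | 7.94 | 51.0% | +0.2 |
| 0.10 | 3.84 | 7.73 | 53.2% | +2.4 |
| 0.15 | 3.73 | 7.51 | 55.5% | +4.7 |
| 0.20 | 3.62 | 7.29 | 58.1% | +7.3 |
| 0.25 | 3.50 | 7.05 | 60.8% | +10.0 |

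Break-even: (1 − R²) × 1.044 = 1 gives R² = 0.043. The two lost degrees of freedom move it to about 0.045.

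**4. A third covariate.** A simulation with 20,000 replicates and three covariates (for example, adding spinal region) gave 48%, 51%, 52%, 57% and 63% at R² 0, 0.05, 0.10, 0.20 and 0.30, against about 51% for the t test. Each added covariate has to earn its cost.

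**5. Chance imbalance.** For a feature present in half the patients, the between-arm difference in its share has SD √(2 × 0.25 / 25) = 0.14. If that feature explains R² 0.10, its two categories differ by 2 × 14 × √0.10 = 8.9 points, so the imbalance moves the estimate by an SD of 8.9 × 0.14 = 1.25 points. The unadjusted SE of 3.96 already includes this.

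**6. Could adjustment rescue 80% power?** By the normal formula, before the penalty, R² would have to be 1 − 25/48.07 = 0.48.

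**The case against.** The strongest reply is that nothing here is an error. An unpaired t test after 1:1 randomisation is valid, no stratification factor is being ignored, and covariates are often left to a statistical analysis plan, which is not shown. Most of this stands, and it is why the point is only an optional improvement. It does not remove the point, because the article is not silent: it fixes the unadjusted tests for all data. If a separate plan adds adjustment, the two texts must agree.

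Four stronger readings are tempting, and the documents do not support them:

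- *Precision is certainly thrown away.* No section links age or number of levels to 24 h QoR-15. Below an R-squared of about 0.045, adjustment loses slightly.
- *The unadjusted estimate is biased by imbalance.* Randomisation makes it unbiased, and its standard error already covers chance imbalance. Adjustment corrects the estimate for the imbalance that happens to occur.
- *Number of levels and region are recorded fields.* The list has only intended surgery. The 2 to 4 range comes from the eligibility criteria, so level count must be coded.
- *Adjustment makes up for the small sample.* It would need an R-squared of about 0.48, which nothing in the protocol suggests.

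It is also fair to object that ANCOVA keeps the target of estimation only on the t-test branch. Mann-Whitney does not estimate a difference in means, so the model has to replace the distribution-test switch for the primary outcome.

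**Conclusion.** The point holds as a low-severity improvement. The plan commits the primary outcome to an unadjusted test while usable pre-allocation covariates are on file and case mix is broad, so precision may be lost. With two covariates the change in power at 25 per arm runs from about −2 points (R-squared 0) to +5 (0.15), +7 (0.20) and +10 (0.25). The trade is asymmetric in favour of adjusting if the covariates are at least moderately prognostic.

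This rests on the protocol's difference of 8 and SD of 14, a two-sided 0.05 test, complete data on 25 per arm, a linear model, and an R-squared that is assumed. The shortfall from 80% to about 51% power on the protocol's own inputs is a different and larger problem, and this change leaves it essentially in place.

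**What to change.** In Statistical considerations, name as primary analysis a linear model (ANCOVA) for 24 h QoR-15 with arm, planned number of operated levels and age. Report the adjusted mean difference with its 95% CI. Say that this replaces the Kolmogorov-Smirnov switch for the primary outcome, and keep the unadjusted comparison as a sensitivity analysis. Add a rule for coding level count from the preoperative intended-surgery entry, applied by someone masked to allocation and never from the operation actually performed. Limit the model to these two covariates.

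All of this must be dated before the randomisation key is released. Recruitment was expected to end on 31 January 2021 and the article appeared on 17 February 2021; it does not say whether the key has been released. If it has, the adjusted result should be labelled as not prespecified.

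Cost: analysis wording and a short coding step, with no new patients or measurements. The downside is two degrees of freedom and about 4% in variance, or about 2 points of power, if the covariates prove uninformative.
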